**Fig. 1 Fig1:**
[figure not shown]
Flowchart of the LION-study

### Participants

The study population consists of community-dwelling SMI patients and SMI patients living in sheltered facilities. Of this population, approximately 75% of the patients is diagnosed with a psychotic disorder, 15% with bipolar disorder and approximately 10% with complex personality disorders. In the North of the Netherlands, SMI patients are invited for annual Routine Outcome Monitoring screenings as part of standard care, consisting of a physical examination, a lab test and psychosocial measures. Patients are invited for the LION study when ROM screening outcomes indicate at least one of the following risk factors for metabolic syndrome: waist circumference > 88/102 cm (females/males); fasting glucose > 5.6 mmol/L or HbA1c > 5.7%; BMI > 25 kg/m^2^. Exclusion criteria are being pregnant, a BMI < 19 kg/m^2^, being primarily diagnosed with Korsakov syndrome or having a physical impairment which makes daily physical activity impossible. When patients are eligible for the study, they receive a detailed information letter from their case manager and, if willing to participate, sign informed consent.

The main objective of this trial is to detect an abdominal weight loss having public health significance. Previous work has indicated that 5-10 cm reduction in waist circumference (WC) is considered a realistic guideline with a high probability of health benefits [32]. For power calculations, we assumed 10% dropout rate. To include 250 participants, a 10% extra will be needed resulting in a total of 275 patients. Under these assumptions, and assuming an SD of 16.3 cm based on pilot data from this population, for two-sided 0.05-level tests of the null hypothesis, the study should provide approximately 80% power for detecting a difference of 5.8 cm in WC at 12 months between intervention and control groups. In addition, the study will have the same power to detect a reduction of 0.6 mmol/L in plasma glucose, given an SD of 1.7 mmol/L.

### Procedure

After patients have signed informed consent, the research coordinator creates a web tool account for the patient. Hereafter, patient and nurse start the intervention by using the web tool ‘Traffic Light Method for somatic screening and lifestyle’ (TLM). The web tool is used during regular care visits, which take place, on average, once every two weeks. During the first visit, patient and nurse map out lifestyle behaviour in the web tool; during later visits they update progress (follow-up) reports (details below). Filling in a follow-up report each biweekly care visit in the follow-up phase is estimated to take 15 min. Six months after start of the intervention, the six-months measures take place. Hereafter, patient and nurse start again with the lifestyle behaviour screening and creating a lifestyle plan, followed by the follow-up phase until the end of the trial (12-months measure).

### Intervention

The intervention in this trial is a 12-month multidimensional, patient-centred lifestyle intervention, including use of the web tool ‘Traffic Light Method for somatic screening and lifestyle’ (TLM), which supports behaviour change in various phases. The five most important features of the intervention are presented in Table 1.

**Table 1 Tab1:** Five important features of the multidimensional lifestyle intervention using a web tool in the LION study

Feature	Description
1	Patients’ readiness for behaviour change is not a prerequisite for starting the intervention. Nurses encourage behaviour change by making use of the stages-of-change of the transtheoretical model [17] and motivational interviewing [16].
2	Patient-centeredness: patients decide if and what behaviour he/she wants to change, creates his/her own lifestyle plan with realistic goals and support. The tool can also be used by patients themselves to enhance self-management.
3	Because diet and physical activity are key components of a healthy lifestyle, these components are combined with behavioural change counselling; for an intervention to be effective, these three ingredients should be included [11].
4	Active support of the patient’s family and friends, incorporated in the lifestyle plan.
5	Nurses are trained to not only support patients in their behaviour change but also work behind the scenes to create a healthier environment: organise accessible exercise opportunities, raise team support for a healthier lifestyle in patients and share up to date lifestyle knowledge with the team, and raise awareness among other health care professionals (e.g. GP’s) of the increased cardiovascular risk of most SMI patients.

The 12-month intervention will be delivered by MH nurses. Before the start of the study, nurses will receive one day of training on (a) basic components of motivational interviewing [16] and the stage of change model [33], (b) side effects of psychotropic medication, (c) lifestyle of and risks for SMI patients, (d) working with TLM, and (e) environmental factors that affect effectively working with TLM (e.g. health behaviour of staff members themselves or the availability of unhealthy products in the home environment) – see Meijel (2015) [25] for more details. In addition, the study protocol will be explained. After three months, an evaluation session is planned to discuss obstacles with the tool, obstacles in motivating patients to participate and to recollect study protocol. Trained LION nurses are, due to the nature of the intervention, not blind for study allocation.

#### Traffic Light Method for somatic screening and lifestyle (TLM)

The Traffic Light Method (TLM) is a web tool originally developed as a practical tool for nurses and patients in one Dutch mental health care organization (GGz Centraal) and further advanced by a small spin-off company (Charly Green, Bilthoven, The Netherlands). It is based on the current state of the art of effective interventions and (inter)national guidelines on healthy lifestyle behaviour. During development, it was extensively reviewed by experts from the field in a Delphi panel and its use was optimized in a pilot study at GGz Centraal [25]. The web tool is, after registration, available online (www.leefstijlinbeeld.nl; for a preview, see Fig. 2a and b).

**Fig. 2 Fig2:**
[figure not shown]
**a** and **b** Preview of the web tool Traffic Light Method (TLM). Legend: **a** the starting page of the lifestyle behaviour screening representing the domains discussed in the Traffic Light Method (TLM) web tool; **b** examples of questions in the dietary domain within the lifestyle behaviour screening with built-in features to increase awareness (colouring according to risk profile) and knowledge (green bars presenting healthy reference values according to (inter)national guidelines)

The TLM consists of two parts: (I) a lifestyle behaviour screening followed by creating a lifestyle plan and (II) a follow-up phase. In the lifestyle behaviour screening, the patient, together with a nurse, answers questions on several health and lifestyle related domains, see Table 2 for an overview of these domains. The Traffic Light Method displays a risk profile with all lifestyle behaviours in green, orange or red, depending on the level of risk. The patient creates, while being coached by the nurse, a lifestyle plan containing maximum three attainable lifestyle goals. During the subsequent follow-up phase, nurse and patient will systematically evaluate the patient’s progress in achieving the lifestyle goals described in the lifestyle plan. This will be done biweekly during regular care visits for approximately 15 min. In order to enhance and stimulate behaviour change, several techniques are built in the web tool. The aims of the lifestyle behaviour screening and the follow-up phase are presented in Table 3.

**Table 2 Tab2:** Domains and subdomains in web tool Traffic Light Method (TLM)

Domain	Subdomains
(a) General medical information	1. Physical measures^a^
	2. Measures from lab test^a^
	3. Physical diseases and handicaps
	4. Rating own health
(b) Use of medication	1. Satisfaction with medication use
	2. Somatic medication
	3. Psychiatric medication
	4. Freely available medication
(c) Dietary habits (last 7 days)	1. Satisfaction with own dietary behaviour
	2. Rating own dietary behaviour
	3. Assessing stage-of-change for dietary behaviour change
	4. Assessing dietary habits
(d) Physical activity (last month)	1. Satisfaction with own physical activity
	2. Rating own physical activity
	3. Assessing physical activity with SQUASH questionnaire
	4. Assessing stage-of-change for physical activity behaviour change
	5. Sedentary behaviour
(e) Use of stimulants	1. Disadvantages of dependence on substances
	2. History of substance abuse
	3. Use of alcohol
	4. Smoking behaviour
(f) Other lifestyle factors	1. Personal hygiene
	2. Relaxation
	3. Sleep behaviour
	4. Computer behaviour
	5. Social environment
(g) Sexuality	1. Condom use
	2. Sexually transmitted diseases
(h) Lifestyle plan^b^	

^a^ Measures are taken from the Routine Outcome Monitoring screening conducted within two months prior to the web tool assessment. ^b^ Only available for participants in the intervention group

**Table 3 Tab3:** Aims for the lifestyle behaviour screening and the follow-up phase in the lifestyle intervention

Aim	Description of aim per phase
Lifestyle behaviour screening phase	
1	Identify unhealthy lifestyle behaviours. The tool uses a traffic light principle for a clear visible presentation of possible health risks related to certain lifestyle behaviours, with green colours representing behaviours with low or no health related risk and red colours representing behaviours with high health related risks (see Fig. 2b).
2	Increase patient’s and nurse’s knowledge of healthy lifestyle behaviours. The tool provides direct feedback on what healthy behaviours are according to (inter)national guidelines and gives additional information to increase patient’s and nurse’s knowledge on healthy lifestyle behaviours (see Fig. 2b).
3	Create awareness. Patients are challenged to discuss identified risk factors and nurses support patients in deciding what lifestyle behaviours to change. Nurses use MI and stages-of-change techniques to assist patients in identifying their problems and overcoming ambivalence or resistance to behaviour change. It is supported by regularly classifying the patient’s current stage-of-change.
4	Create a lifestyle plan with concrete and reachable goals. Based on the lifestyle anamnesis and discussion with the nurse, patients set maximum three goals to achieve according to the criteria of S.M.A.R.T.-goals [58]. The nurse’s role is to support patients in setting realistic goals. Patients explore which interventions are available and seem attractive, and what is needed to reach goals. Active self-management of patients is encouraged, support of family and friends is explored and, when available and deemed necessary, incorporated in the plan.
Follow-up phase	
6	Evaluating lifestyle goals systematically on a regular basis. During every regular care visit, a new follow-up file is uploaded and filled in by patient and nurse. By doing this, continuity is ensured and this repetitive character will lead to more sustainable behaviour change.
7	Barriers and facilitators in achieving lifestyle goals are indicated. Patient and nurse discuss which factors are helpful in achieving goals and which factors limit achieving goals in order to increase the success of achieving the goals in the following period. Again, nurses use motivational interviewing techniques and the stages-of-change of the transtheoretical model.

All information entered in the web tool can be printed as a personal booklet for the participant to share the information and his/her lifestyle plan with friends and family or to use healthy lifestyle information in daily life (such as when doing groceries, preparing food).

#### Implementation strategy

To increase the degree of implementation of the intervention, an implementation strategy was defined consisting of several components: 1) establish support from organizational management, 2) involve team management, 3) train MH nurses in using the web tool, motivational interviewing and the stage of change model, 4) plan a meeting with MH nurses and the trainer three months after training, 5) plan regular visits of research team one every three months, 6) send out newsletters to keep teams and nurses informed and involved.

### Control group

Patients in the control group participate in ROM screenings and results are discussed with the patient as part of standard care. Because data on lifestyle behaviours will be gathered from the lifestyle anamnesis part in the web tool, patients in the control group fill in the questions in the anamnesis part of the tool, but in blanc version in the web tool or on paper version; they do not receive any feedback or information via colours or education rules. In addition, patients in the control condition do not set up a lifestyle plan and therefore have no biweekly follow-up sessions. Nurses in the control group are instructed to give care as usual. This implies medical problems are tackled immediately according to protocol, while lifestyle guidance is more or less provided when patients wish to (based on ROM screenings).

### Outcomes

Measurements are performed on patient and staff level. An overview of all measurements at baseline, six and twelve months is given in Table 4.

**Table 4 Tab4:** LION trial measurement overview

		Baseline	6 months	12 months
Measurements on patient level				
Routine Outcome Monitoring				
General information	Birth year, gender, diagnoses, year of first psychosis	X		
	Medication use	X		X
Physical measures	Height	X	X	X
	Weight	X	X	X
	Waist circumference	X	X	X
	Blood pressure (systolic, diastolic, pulse)	X	X	X
Lab test	Lipids (Total cholesterol, LDL-cholesterol, HDL-cholesterol, triglycerides)	X	X	X
	Glucose metabolism (glucose, HbA1c)	X	X	X
Psychological measures^b^	CDSS	X		X
	PANSS	X		X
	HoNOS	X		X
	MANSA	X		X
Cost-effectiveness^a^	Dutch care consumption questionnaire	X	X	X
	SF6D	X	X	X
Web tool TLM				
Lifestyle habits	Daily physical activity (SQUASH)	X	X	X
	Food frequency questionnaire (adapted to patient population)	X	X	X
Additional measure by research assistant				
	Physical activity (pedometers) and body fatness^c^	X	X	X
Measurements on staff level				
General information	Birth year, gender, level of education, number of years working in psychiatry, function	X		
Staff questionnaire	Knowledge on diet and physical activity, attitude towards lifestyle changes in patients, self-efficacy in addressing lifestyle issues with patients	X		X
	Daily physical activity (SQUASH)	X		X
	Food frequency questionnaire	X		X

^a^ Measures are not part of standard ROM screening but added to ROM screening for the purpose of this study. ^b^ The conducted psychosocial measures within the ROM protocol could vary per team, not all teams conduct every psychosocial measure. ^c^ Only conducted by one of the five health care organisations (GGZ Friesland)

#### Measurements on patient level

Most measures on patient level are conducted during the ROM screening, which is part standard care and of the scientific ongoing PHAMOUS (Pharmacotherapy Outcome and Monitoring Survey) cohort [34]. In mental health care organisations in the North of the Netherlands, it is routine care that ROM trained nurses invite patients annually for a ROM screening including somatic and psychosocial measures. Data of these measurements are reported in patients’ record forms and discussed with the patient. These data are stored in a large database and anonymized data are available for scientific research. This method was approved by the Medical Ethical Committee of the University Medical Center Groningen. For the LION study, data of two regular ROM screenings will be used for baseline and 12-months measures. An additional, short version of the ROM screening is scheduled six months after start of the intervention and patients will receive a small fee (€5,00/£4,30) for participation. ROM nurses carrying out the assessments are blinded for study allocation.

General data on birth year, gender, diagnosis, duration of illness and use of medication are derived from patient record forms.

#### Cardiometabolic health

The physical measurements include waist circumference, height, weight, pulse and systolic and diastolic blood pressure. Patients visit a (hospital) laboratory that collects a blood sample, if possible in fasting state, for levels of lipids (total cholesterol, LDL-cholesterol, HDL-cholesterol and triglycerides [all in mmol/L]) and glucose metabolism (glucose [mmol/L], HbA1c [%]). Measurements are taken following standard ROM protocols. Waist circumference (in cm) is measured in duplicate using a flexible nonstretching tape halfway between the iliac crest and lowest rib in standing position at the end of an expiration. Body weight is measured by calibrated scales (Seca, model 813) in light clothing without shoes or jackets. Measurements for height (in cm) will be available from multiple measurements of ROM nurses. The highest height will be used unless patients wear shoes, then the highest height without shoes is used. Pulse and systolic and diastolic blood pressure are measured after 5 min’ rest in sitting position, using a blood pressure monitor (BOSO medicus control).

#### Mental health

During an interview, trained nurses administer positive and negative symptoms with the PANSS (Positive and Negative Syndrome Scale [35]) and depressive symptoms with the CDSS (Calgary Depression Scale for Schizophrenia [36]). Prior to the interview, patients fill in the MANSA, a self-report questionnaire about patients’ Quality of Life [37] and uncertainties can be discussed during the interview. The HoNOS (Health of the Nations Outcome Scale [38]) is an observation scale of psycho-social functioning and is scored by the case manager or team.

#### Lifestyle habits

LION trained nurses assess lifestyle habits using the lifestyle behaviour screening part in the web tool TLM. Items in the TLM physical activity and nutritional domain serve both a measurement purpose as well as an intervention purpose. Daily physical activity is assessed using the Dutch validated SQUASH questionnaire [39]. Nutritional habits are estimated using a semi-quantitative food frequency questionnaire (FFQ) with items based on a screening questionnaire for healthy eating habits of the Netherlands Nutrition Center according to the Dutch guidelines for a healthy diet [40] and adapted to this population. The questionnaire will be used to assess changes in dietary habits on food group level. It is not specifically validated in SMI patients and can and will not be used to derive quantitative estimates of total energy, macro- or micronutrient intake.

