### Statistical analysis

Variables will be presented as mean ± standard deviation (SD), and if not normally distributed as median [25th-75th percentiles], or N (%) for frequencies. Missing data are handled differently based on amount and type of missingness. If missing data can be well predicted by regression methods, multiple imputation will be considered. Otherwise, interpolation or replacement by study mean or median will be preferred over complete case analyses.

The primary outcome is the change in waist circumference (in cm) over time (from baseline to six and from baseline to twelve months) comparing the intervention group to the control group. This will be analysed with multilevel linear mixed models using teams as cluster. Analysis will be based on intention-to-treat principle. In per-protocol analyses, the intervention effect on cardiometabolic risk factors will be studied as described above, comparing participants with different degrees of intervention adherence to controls. Secondary study outcomes are analysed according to the same principles and techniques as the primary outcome. A priori sensitivity analyses are foreseen for participants’ age, gender and type of housing. In additional analyses, we will test whether the 12-months lifestyle intervention changes the level of motivation (stage-of-change) for changing diet of physical activity levels. An alpha of 0.05 is considered statistically significant.

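### Self-reported lifestyle habits and stage-of-change are collected with a coloured, coached tool in one arm and a blank form in the other, so arm differences in these additional outcomes can partly reflect the measurement format

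*Protocol article*

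**What the plan says.** All places are in the protocol article.

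- **Source of the data.** The Control group section says that "data on lifestyle behaviours will be gathered from the lifestyle anamnesis part in the web tool", and this covers both arms. Under Outcomes, Lifestyle habits: "LION trained nurses assess lifestyle habits using the lifestyle behaviour screening part in the web tool TLM". The same paragraph adds that "Items in the TLM physical activity and nutritional domain serve both a measurement purpose as well as an intervention purpose".
- **Intervention arm.** The section on the Traffic Light Method has patient and nurse answering together: "The Traffic Light Method displays a risk profile with all lifestyle behaviours in green, orange or red, depending on the level of risk". Table 3, aim 2, lists feedback as a goal of the screening phase itself: "The tool provides direct feedback on what healthy behaviours are according to (inter)national guidelines". The Fig. 2 legend describes green bars with reference values shown at the questions. The Intervention section says that the trained nurses are not blind to allocation. The Procedure section places the first screening inside the visit at which the intervention starts.
- **Control arm.** Patients answer the same questions, "but in blanc version in the web tool or on paper version", and "they do not receive any feedback or information via colours or education rules".
- **Use.** Table 4 schedules SQUASH and the food frequency questionnaire at baseline, 6 and 12 months. The Lifestyle habits section uses the food questionnaire to assess dietary change. Among the additional analyses in Statistical analysis: "we will test whether the 12-months lifestyle intervention changes the level of motivation (stage-of-change".

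**The concern.** An arm comparison of a self-reported score assumes that the score is obtained in the same way in both arms. Here three things differ by arm at the moment of answering: what the screen shows, whether a coaching nurse takes part, and possibly the medium (web or paper). A patient who sees an answer turn red, or sees the recommended value beside the question, may answer differently from one who sees neither, with no difference in behaviour.

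At stake is the reading of reported activity, reported diet and readiness to change. Each could show a difference that partly belongs to the form, or hide a real one. The section on potential risks for bias does not mention this.

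**Working it through.** The plan states no figure on this point, so the check sets the passages side by side and then asks what survives in the planned analysis.

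**Step 1: the arms compared**

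| Feature at a TLM assessment | Intervention | Control |
|---|---|---|
| Form | full web tool | blank web version or paper |
| Risk colours | yes | no |
| Guideline feedback | yes | no |
| Who answers | patient with coaching nurse | patient fills in the questions |
| Baseline | first visit of the intervention | blank version |

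The last two control entries rest on the Control group section alone. The Lifestyle habits section speaks of trained nurses assessing lifestyle habits without separating the arms, so the control mode of administration is not fully clear.

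**Step 2: what survives in change from baseline**

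The primary outcome is analysed as change from baseline, and secondary outcomes follow the same principles. Suppose this also holds for the TLM outcomes. In the intervention arm, let f0 be the effect of the coloured, coached form on the baseline answer and f12 its effect at 12 months. Let r be any further shift in reporting from having learned the favourable answers and been coached between visits. Controls have none of these. Then:

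observed arm difference in change = true difference + (f12 − f0) + r

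- If f12 = f0, the format effect cancels and only r is left.
- If f12 is larger than f0, the bias favours the intervention.
- If f0 is larger than f12, the bias runs against it.
- Stage-of-change has five ordered categories, so the form's effect need not be additive or equal at repeat use. Partial cancellation is the safe statement.

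The documents give no value for f0, f12 or r, so neither size nor direction can be derived.

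**Step 3: sensitivity, by assumption only**

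Let b be the net bias that remains, f12 − f0 + r, in SD units of the analysed score. Take 250 analysed patients (Participants section), equal allocation (assumed, 125 per arm), two-sided alpha 0.05, no true effect and no clustering.

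- Standard error = √(2/125) = 0.126 SD, and z = b/0.126.
- Rejection rate = Φ(z − 1.96) + Φ(−z − 1.96).

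| b (SD) | 0 | 0.1 | 0.2 | 0.3 | 0.4 |
|---|---|---|---|---|---|
| Significant difference | 5% | 12% | 35% | 66% | 89% |

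This shows how sensitive the test is to a remaining shift. It does not estimate the shift. An analysis that allows for team clustering has a larger standard error, so its rates would be lower at the same b.

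**Step 4: which outcomes are touched**

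The section on measurements on patient level has blinded ROM nurses carry out the ROM assessments. Waist circumference, weight, blood pressure and laboratory values come by that route and not through the TLM. Pedometer steps and body fat are also collected outside the tool, at all three time points, but in one of the five organisations only (Table 4, footnote c; Physical fitness).

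**The case against.** **The outcomes are minor.** This stands. Lifestyle habits and stage-of-change appear in none of the research questions, and the stage-of-change test is an additional analysis. A reader might infer that the waist result is compromised. The documents do not support that, because waist is measured by blinded nurses outside the tool.

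**No mechanism analysis is planned.** This also stands. A reader might infer that the bias would misstate why the trial worked or failed. The Statistical analysis section contains no mediation analysis. The hypothesis at the end of Aims of the trial bases the waist effect on activity and diet, not on stage-of-change.

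**Item order proves little.** In Table 2 the activity stage-of-change item follows the SQUASH, which suggests that it is answered after feedback. In the dietary domain the stage item comes before the habit items, and nothing says that the list is the screen order. Nor does Table 4 list stage-of-change, so its timing is inferred from its place in the screening.

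**A constant format effect cancels.** This stands in part, as Step 2 shows. It means that no false-positive rate can be claimed for this trial. It does not remove r or a changing f.

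**Feedback while answering is part of the product, and a display switch leaves the coaching effect.** Both are true. The switch removes the format difference only, and the rest has to be dealt with by labelling.

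**Conclusion.** The concern holds in a limited form. The protocol article itself establishes that the TLM answers are outcome data and intervention at once, and that display, feedback and nurse involvement differ by arm. Arm differences in SQUASH, food questionnaire and stage-of-change scores can therefore partly be measurement. The size and sign of the bias are unknown, and change from baseline removes some of it if the format effect is stable. The percentages in Step 3 depend wholly on an assumed remaining shift. The trial's conclusion on waist circumference and the other ROM measures is untouched. The change is worth making because it is cheap and the blank version already exists, not because the main result is at risk.

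**What to change.** 1. At each scored TLM assessment, have both arms complete the existing blank version in the same mode. Lock the answers, and only then release colours, feedback and the lifestyle plan in the intervention arm. Analyse only the locked answers.
2. Apply this from baseline onward in each patient and record which version was used. A coloured baseline followed by a blank follow-up would leave −f0 in the change score and lose the cancellation.
3. Label the TLM-derived outcomes, including the stage-of-change test, as exploratory. Say in the section on risks for bias that they are self-reported with an unblinded coaching nurse, and that answers learned through coaching may persist at 6 and 12 months.
4. Read reported activity beside the pedometer data from the one organisation that collects them, as a partial check.

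The cost is a display switch in the web tool, a short nurse instruction and a sentence or two of text. The downside is that intervention patients see the feedback minutes later, within the same visit, instead of while answering. For assessments already taken in the present format, only items 3 and 4 and the record of version remain available.
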